### 2.2. Sample Size

As this is a prospective pilot study, the planned sample size was not based on a formal confirmatory power calculation. Currently, there is limited data allowing for a reliable estimation of the expected effect size for the association between baseline fatty acid profiles and antidepressant treatment outcomes. Therefore, the planned recruitment of 60 participants was determined pragmatically, based on the feasibility of recruitment, follow-up, and biological sample processing and on the aim of obtaining preliminary estimates of variability, effect sizes, responder proportions, and attrition rates for a future adequately powered study. Based on previous studies, the anticipated treatment response rate is approximately 50% [24]. Therefore, before accounting for attrition, the planned sample of 60 participants may yield approximately 30 responders and 30 non-responders. This estimate is provided to describe the expected sample distribution and does not imply that the study is adequately powered to develop or validate a multivariable prediction model [25].

### 2.3. Scales and Questionnaires

A study questionnaire (SQ) will be used to collect basic socioeconomic data as well as various health-related information. Participants will be asked to provide, among other things, personal details, place of residence, and occupation, as well as information on dietary supplement use, current medications, smoking habits, chronic diseases, and psychotherapy. Use of medications or supplements potentially affecting lipid metabolism, inflammatory status, or gut microbiota composition, including statins, corticosteroids, antibiotics, probiotics, and omega-3 supplements, will also be recorded. For participants receiving antidepressant treatment, the SQ will also record medication class (SSRI, SNRI, or others), dose expressed as fluoxetine equivalents, and use of combination therapy. As most participants will be inpatients at baseline, adherence to antidepressant pharmacotherapy is expected to be high during the initial phase of treatment and will be monitored as part of routine clinical care. Following discharge, participants will be provided with a structured medication adherence form, on which they will be asked to record each administered dose on a daily basis. Completed forms will be collected and reviewed at each subsequent follow-up time point. These variables will be described and, depending on their frequency and data distribution, considered as potential confounders in analyses of treatment response.

Beck Depression Inventory-II (BDI-II) is a widely used self-report questionnaire designed to assess the severity of depressive symptoms in adolescents and adults. The instrument consists of 21 items, each reflecting a specific symptom or attitude related to depression, in accordance with diagnostic criteria for depressive disorders. Respondents are asked to rate how they have been feeling over the preceding two weeks, including the day of assessment. Each item is scored on a 4-point scale ranging from 0 to 3, with higher total scores indicating greater severity of depressive symptoms. The total score ranges from 0 to 63 and is interpreted using established cut-off values: 0–13 indicating minimal, 14–19 mild, 20–28 moderate, and 29–63 severe depressive symptoms [26].

The BDI-II captures three key dimensions of depression: the cognitive dimension, reflecting negative thoughts, pessimism, and self-evaluation; the affective dimension, encompassing mood disturbances such as sadness and loss of pleasure; and the somatic dimension, addressing physical symptoms including changes in sleep, appetite, energy levels, and psychomotor functioning [27].

The Polish version of the Beck Depression Inventory-II (BDI-II), which has been psychometrically validated for internal consistency, construct validity, and criterion validity in a Polish population, will be used to assess depressive symptom severity [28].

Depression, Anxiety, Stress Scales (DASS-42) is a self-report instrument designed to assess the severity of symptoms related to depression, anxiety, and stress in adults. The scale consists of 42 items, divided into three subscales, each comprising 14 items: Depression, Anxiety, and Stress [29].

The Depression subscale assesses dysphoria, hopelessness, lack of interest, self-deprecation, and anhedonia. The Anxiety subscale focuses on autonomic arousal, skeletal muscle effects, situational anxiety, and subjective experiences of anxious affect. The Stress subscale measures chronic non-specific arousal, including difficulty relaxing, irritability, nervous tension, and agitation.

The Polish validated version of the Depression Anxiety Stress Scales (DASS-42), developed by Makara-Studzińska et al., will be used in this study [30].

WHO Quality of Life (WHOQOL-BREF) is a standardized self-report questionnaire developed by the World Health Organization to assess subjective quality of life in adults. It is a shortened version of the WHOQOL-100 and consists of 26 items. The instrument measures quality of life across four domains: physical health, psychological health, social relationships, and environment, as well as two general items assessing overall quality of life and general health perception. Participants rate each item on a 5-point Likert scale, reflecting intensity, capacity, frequency, or evaluation. Domain scores are calculated according to WHO guidelines, with higher scores indicating better perceived quality of life [31]. The study will use the Polish validated version of the WHOQOL-BREF questionnaire by Jaracz et al. [32].

The Frequency Questionnaire (FFQ-6) is a dietary assessment tool designed to evaluate habitual food consumption patterns over a specified retrospective period. The questionnaire focuses on the frequency of intake of selected food groups. Participants are asked to report how often they consume specific food items or food categories using predefined frequency options. The FFQ-6 enables estimation of dietary patterns, nutrient intake proxies, and adherence to specific dietary behaviors, including those relevant to lipid and fatty acid intake. The study will use the Polish validated version of the FFQ-6 questionnaire by Niedzwiedzka et al. [33].

Dietary data obtained from the FFQ-6 will be aggregated into predefined food groups for the purpose of statistical adjustment. The following groups will be distinguished: sweets and snacks, dairy and eggs, cereal products, oils, fruits, vegetables and seeds, meat (including fish and its subcategories of processed and unprocessed meat), alcohol, and drinks excluding water. Selected groups will be further subdivided into processed and unprocessed subcategories. For each group, a dietary index will be calculated based on the mean consumption frequency of constituent products. A composite processed food index will additionally be derived from items classified as processed across multiple food categories. These indices will serve as dietary covariates in regression analyses examining fatty acid profiles in relation to clinical outcomes [34].

The International Physical Activity Questionnaire (IPAQ) was developed by an international consortium to provide a standardized measure of physical activity suitable for international and cross-cultural use. A large reliability and validity study conducted across 12 countries (including translation and cultural adaptation procedures) showed acceptable measurement properties [35]. The study will use the Polish version of the IPAQ compiled by Biernat et al., which has been officially translated and registered for use in Poland and enables classification of physical activity into internationally standardized MET-minute categories [36].

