## 2. Materials and Methods

### 2.1. Study Design and Population

This protocol was prepared following the Standard Protocol Items: Recommendations for Interventional Trials (SPIRIT) 2025 guidelines, adapted to the extent applicable to the observational prospective design of the present study [23].

Participants will be recruited in the Central Teaching Hospital of the Medical University of Lodz, primary healthcare clinics, and mental health clinics in the Lodz voivodeship. The study population will consist of 60 adults diagnosed with depressive disorders according to the International Classification of Diseases, 11th (ICD-11). Eligible diagnoses will include single-episode depressive disorder, recurrent depressive disorder, and dysthymic disorder, reflecting the spectrum of conditions characterized primarily by depressive symptomatology. Additionally, participants must present with a BDI-II score ≥ 15 at baseline, confirming clinically relevant depressive symptom severity at the time of enrollment.

Each participant will be at the beginning of a new pharmacological antidepressant treatment (5 days before to 5 days after treatment initiation). Antidepressant treatment will not be standardized by the study protocol, as treatment decisions will follow routine clinical practice. Antipsychotic medication used as augmentation of antidepressant treatment will not constitute an exclusion criterion but will be recorded as a combination treatment.

To qualify for the study, participants must meet all inclusion criteria and not meet any exclusion criteria listed in Table 1.

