During the study, each participant will have a scheduled on-site visit, during which questionnaires will be completed, and blood samples will be collected for analysis. After centrifugation, serum aliquots and washed erythrocyte pellets will be frozen and stored under predefined biobanking conditions. Following this visit, three subsequent time points are planned—at 3, 6, and 12 weeks (follow-up)—during which the participant will receive online questionnaires to complete. Follow-up assessments will be scheduled relative to the date of antidepressant treatment initiation. At each follow-up assessment, participants will report current antidepressant treatment, dose changes, discontinuations, augmentation strategies, newly introduced concomitant medications, and psychotherapy participation. Participants will remain in the study if the antidepressant treatment is modified during follow-up. The type, date, and reason for each treatment modification will be recorded. A sensitivity analysis will be performed after excluding participants with major treatment modifications before the week 6 assessment. The time points’ schedule is also illustrated in Figure 1.

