Antidepressant class will initially be categorized as selective serotonin reuptake inhibitor, serotonin–norepinephrine reuptake inhibitor, or other. Categories may be combined if their sizes do not permit reliable estimation. The robustness of the primary findings will be examined in sensitivity models additionally accounting for relevant dietary, metabolic, lifestyle, and treatment-related factors. These may include fish and seafood intake, a plant- and fiber-rich food index, body mass index or waist circumference, physical activity, smoking, alcohol consumption, comorbidities, concomitant medications, psychotherapy, adherence, hospitalization status, and treatment modifications. Because of the limited sample size, these variables will not all be included simultaneously in a single model. Secondary binary outcomes at week 6 will include treatment response, remission, and minimal clinically important improvement. Their associations with individual fatty acids will be examined using separate exploratory logistic regression models with a limited number of prespecified covariates. Penalized likelihood estimation may be used in the event of complete or quasi-complete separation. 

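### The daily dose form is issued only at hospital discharge, so participants who are never admitted are assigned no dose-level adherence record and the optional adherence covariate would depend on care setting

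*Protocol article*

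**What the plan says.** Section 2.1 recruits from a teaching hospital and also from "primary healthcare clinics, and mental health clinics in the Lodz voivodeship". Section 2.3 opens its account of adherence with "As most participants will be inpatients at baseline", so some participants are expected not to be inpatients. It then says that adherence "is expected to be high during the initial phase of treatment and will be monitored as part of routine clinical care".

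The study's own instrument comes next: "Following discharge, participants will be provided with a structured medication adherence form". This is a diary that participants keep themselves; the instruction is that "they will be asked to record each administered dose on a daily basis". Its return is described as "Completed forms will be collected and reviewed at each subsequent follow-up time point". For those follow-up points, section 2.1 describes contact "during which the participant will receive online questionnaires to complete".

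Section 2.1 also has every participant report at each follow-up which antidepressant is being taken and whether it was changed in dose or stopped. The kind, date and reason of each modification are recorded.

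In the analysis, section 2.3 treats these variables as possible confounders, subject to how often they occur and how they are distributed. Section 2.6 names candidates for the sensitivity models, among them "concomitant medications, psychotherapy, adherence, hospitalization status, and treatment modifications". The primary model in 2.6 contains time, the fatty acid, their interaction, age, sex and antidepressant class. It does not contain adherence.

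**The concern.** The stated trigger does not fit the stated population. A participant recruited at a clinic and never admitted is never discharged, so the rule gives the site no moment at which to issue the form. These participants take their doses without supervision from the start. Inpatients do receive the form, but only from discharge, and the article does not say that their in-hospital dosing becomes study data.

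Missed doses are an obvious competing explanation for non-response to a newly started drug, which is presumably why adherence is on the list of sensitivity covariates. If the dose-level measure exists only for people who were once in hospital, a model adjusted for it either loses the never-admitted participants or assigns them an assumed value. A shift in the fatty-acid estimate between the primary and the adjusted model could then come from the change of sample rather than from the adjustment. Dose records not kept during follow-up cannot be rebuilt at analysis.

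**Working it through.** The plan states no figure on this point, so there is none to reproduce. The check sets the rules side by side and then works through the only arithmetic available, on stated assumptions.

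**What each group has, from treatment start to week 6, under the text as written**

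| Group | Dose-level study record | Other information |
|---|---|---|
| Never admitted | No form assigned (2.3 gives discharge as the only trigger) | Self-report of treatment, dose changes and stopping at weeks 3 and 6 (2.1) |
| Inpatient, discharged before week 6 | Form from discharge to week 6 | Routine ward monitoring before discharge; the same self-report |
| Inpatient, still admitted at week 6 | None before the primary time point | Routine ward monitoring; the same self-report |

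The self-report shows that a drug was stopped or changed. It does not show doses missed while the prescription continued, which is what the daily form is for.

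**Effect on the sensitivity covariate.** Suppose adherence is taken from the form and analysed on complete cases. The never-admitted group then has no value and drops out. If hospitalization status means inpatient or not at baseline, and all participants with a form were inpatients then, status no longer varies in the remaining sample, so the two listed covariates cannot be separated. Both definitions are assumptions, since the article fixes neither.

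**Number without a form.** Inputs: N = 60 (section 2.2); outpatient share p is not given.

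- Number = p × 60.
- p = 10%: 0.10 × 60 = 6.
- p = 40%: 0.40 × 60 = 24.

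**Days covered by the form for inpatients.** Inputs: follow-up is timed from treatment initiation (2.1), so the window to week 6 is 6 × 7 = 42 days; the in-hospital time after treatment start, L days, is not given.

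- Days covered = 42 − L; share = (42 − L)/42.
- L = 14: 28 days, 67%.
- L = 28: 14 days, 33%.
- L = 42: 0 days, 0%.

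These figures show how the rule behaves over a range. They do not estimate actual loss.

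**The case against.** The strongest reply is that section 2.3 describes the usual pathway and is silent on the minority outside it. Silence is not exclusion, and a journal article may leave to the full protocol when a form is handed to a subgroup. This stands in part: the text does not forbid giving the form to outpatients. But the article does describe the form, its content, its trigger and its return, and the trigger it states cannot occur for some of the people it recruits. That is a stated rule that needs correcting, not a detail left out.

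Several stronger readings are tempting, and the documents do not support them:

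- **That outpatients are not monitored for adherence at all.** Section 2.1 collects treatment status, dose changes and discontinuations from everyone at weeks 3, 6 and 12. The gap is missed doses.
- **That inpatients go unmonitored.** Section 2.3 assigns that phase to routine clinical care. What is open is whether it becomes study data.
- **That the plan commits to an adherence-adjusted model for all participants.** Section 2.6 says only that the sensitivity models may draw on the listed factors, and that they will not all enter one model. No committed analysis is broken.
- **That collecting a daily form contradicts online follow-up.** A form can be returned remotely. The article does not state the route, but nothing conflicts.
- **That the primary result is biased.** Adherence is not in the primary model. The exposure is baseline fatty acids, so later non-adherence would distort that association only if it were related to fatty-acid level, which nothing in the document establishes.

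**Conclusion.** The point holds in a limited form. Discharge is the only stated trigger for the dose form, while recruitment includes outpatient clinics and only a majority of participants are expected to be inpatients. As written, never-admitted participants are assigned no dose-level record, and inpatients have a study-kept one only from discharge. An adherence covariate built on the form would differ in availability by care setting and could not be cleanly separated from hospitalization status.

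The consequence is confined to optional, exploratory sensitivity models. The primary contrast stands as planned. The size cannot be fixed from the document: 6 to 24 of 60 without a form rests on an assumed outpatient share of 10% to 40%, and 28, 14 or 0 of 42 days covered rests on assumed stays of 2, 4 or 6 weeks. The point deserves action because the correction is cheap and works only if made before the data are collected.

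**What to change.** In section 2.3, replace the single discharge trigger with three statements:

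1. Every participant who is not an inpatient receives the existing form at the baseline visit, or at the first dose if that is later. Inpatients receive it at discharge, as now.
2. The form is returned with the online questionnaires at weeks 3, 6 and 12.
3. In-hospital days are treated as supervised dosing, using existing ward medication records where available, so that one adherence measure runs from treatment start to week 6 for all participants.

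Because enrolment is allowed up to 5 days after treatment start, a form issued at baseline can miss up to 5 of the 42 days (5/42 = 12%). A line for those earlier doses, completed at the visit, would close that gap.

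Cost: a few sentences in 2.3, earlier issue of a form that already exists, and a slight diary burden for outpatients. Using ward records adds some work at the hospital, which is why it is limited to records already kept. Neither treatment nor the primary model changes.

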### 2.4. Biological Parameters

Physical examination parameters: weight, body mass index (BMI), and waist circumference (WC).

Anthropometric indicators such as BMI and waist circumference are essential covariates in research examining circulating fatty acid levels.

BMI provides a general estimate of overall adiposity, which influences lipid metabolism, fatty acid storage, and mobilization. Individuals with higher adiposity often present altered profiles of circulating fatty acids due to changes in lipid turnover, insulin sensitivity, and adipose tissue function. Waist circumference, in contrast, is a specific marker of visceral fat accumulation, which is metabolically more active than subcutaneous fat.

Visceral adiposity is strongly associated with disruptions in lipid homeostasis, increased lipolysis, and elevated flux of free fatty acids into the bloodstream. Consequently, it may significantly modify the concentrations of fatty acids measured in plasma or serum [37].

Blood samples will be collected in the morning after an overnight fast by qualified medical personnel. CRP and complete blood count will be assessed in all participants using blood collected during the baseline visit. The neutrophil-to-lymphocyte ratio will be calculated as the absolute neutrophil count divided by the absolute lymphocyte count.

To obtain serum, blood will be collected into tubes without anticoagulants or preservatives and kept in an upright position at room temperature for 30–45 min to allow for clot formation. The samples will then be centrifuged for approximately 10–15 min at 3000× *g*. After centrifugation, the serum will be carefully aspirated and transferred into patient code-labeled cryovials.

To obtain the erythrocyte pellet for FAME analysis, blood will be collected into tubes containing ethylenediaminetetraacetic acid (EDTA) and gently mixed immediately after collection. The samples will then be centrifuged for approximately 10–15 min at 3000× *g*. After centrifugation, the plasma will be carefully aspirated in order to isolate the pellet which will be washed twice with isotonic saline to remove residual proteins and transferred into patient code-labeled cryovials.

Post-centrifugation pellet samples will be frozen and stored in the Biobank.

The samples will be transported on dry ice from the Medical University of Lodz to the collaborating laboratories.

Samples will be identified exclusively by study codes, and laboratory personnel will not have access to personal identifiers or treatment outcome data.

Blood will be collected to determine the profile of short-chain fatty acids in serum as well as the erythrocyte membrane medium- and long-chain fatty acid composition. The simultaneous assessment of erythrocyte membrane fatty acids and serum short-chain fatty acids reflects the complementary and mechanistically distinct roles these lipid fractions play in depression pathophysiology. Erythrocyte membrane fatty acid composition—particularly the balance of n-6 and n-3 polyunsaturated fatty acids—provides an integrated index of long-term fatty acid status and membrane-level inflammatory potential, reflecting dietary intake and metabolic processing over the preceding 90–120 days [38]. In contrast, serum SCFAs represent dynamic, rapidly fluctuating metabolites produced by gut microbiota fermentation, serving as proxies of gut microbial activity and gut–brain axis signaling at the time of assessment [39]. By capturing both long-term structural fatty acid status and acute microbial metabolite levels within the same participants, this study aims to provide a comprehensive and mechanistically grounded characterization of the lipid-related biological landscape associated with depressive disorders and antidepressant treatment response.

Certified reference standards of saturated, monounsaturated, and polyunsaturated fatty acids ranging from C10 to C24 will be used, including decanoic (C10:0), undecanoic (C11:0), lauric (C12:0), myristic (C14:0), myristoleic (C14:1), pentadecanoic (C15:0), palmitic (C16:0), palmitoleic (C16:1), margaric (C17:0), heptadecenoic (C17:1), stearic (C18:0), vaccenic (C18:1n7), oleic (C18:1n9), linoleic (C18:2n6), γ-linolenic (C18:3n6), α-linolenic (C18:3n3), arachidic (C20:0), eicosenoic (C20:1), eicosatrienoic (C20:3n6), arachidonic (C20:4n6), eicosapentaenoic (C20:5n3), behenic (C22:0), erucic (C22:1n9), docosatetraenoic (C22:4n6), docosapentaenoic (C22:5n3), docosahexaenoic (C22:6n3), tricosanoic (C23:0), lignoceric (C24:0), and nervonic (C24:1) acids. Heneicosanoic acid (C21:0) will be used as an internal standard.

FAMEs will be extracted from the erythrocyte pellet using a modified Folch procedure. Samples will be mixed with chloroform and methanol (2:1, *v*/*v*), followed by the addition of the internal standard and butylated hydroxytoluene. The mixtures will be agitated for 20 min and centrifuged, after which the supernatant will undergo saponification with potassium hydroxide in methanol at approximately 70 °C, followed by methylation using boron trifluoride in methanol under the same conditions. After derivatization, FAMEs will be extracted into hexane following the addition of saturated sodium chloride solution and transferred to chromatographic vials.

Gas chromatographic analysis will be performed using an Agilent 7890A system (Agilent Technologies, Santa Clara, CA, USA) equipped with a Supelcowax™ 10 capillary column. A defined oven temperature program will be applied, with hydrogen used as the carrier gas at a constant flow rate. Fatty acids will be identified by comparison of retention times with authentic standards, and quantitative analysis will be conducted using the ChemStation LTS 01.11 software, with relative fatty acid concentrations calculated in reference to the internal standard. The analytical procedure will follow established lipidomic methodologies.

Serum concentrations of acetate, propionate, and butyrate will be quantified using gas chromatography–mass spectrometry at the Institute of Food Technology and Analysis, Lodz University of Technology. These three SCFAs were selected as they represent the most abundant products of anaerobic fermentation of dietary fiber by the gut microbiota, collectively accounting for over 90% of total SCFA production in the human colon, and have been most consistently implicated in gut–brain axis signaling and neuroinflammatory modulation relevant to depressive disorders.

The analysis of SCFAs will be performed on a GCMS-2010 (Shimadzu Corporation, Kyoto, Japan). A split/splitless injector will be set to 200 °C. The temperature program will be as follows: 100 °C (3 min hold) ramped to 210 °C (0.5 min hold) at 30.0 °C min^−1^. Helium will be used as the carrier gas at a constant linear velocity of 50 cm s^−1^ (with an initial inlet pressure of 133.0 kPa). The injection volume will be 8.0 μL with a split ratio of 1:5.

The MS system will operate in electron ionization (EI) mode using an ionization energy of 70 eV, and it will acquire the target compounds in selected ion monitoring (SIM) mode, monitoring three different fragment ions for each compound within specific time acquisition windows. The following ions will be selected: propionic acid, 74 *m*/*z* (Q); acetic acid, 60 *m*/*z* (Q); and butyric acid, 88 *m*/*z* (Q). MS parameters will be set as follows: an ion source temperature of 220 °C and interface temperature of 220 °C. The GCMS solution software 4.45 will be used for both data acquisition and processing.

To ensure the quality of the analyses, four replicates will be performed. The scan mass range will be 30–400 *m*/*z*. Compound identification will be performed using commercial standard kits. Prior to analysis, a system suitability test will be performed by injection. Five replicates will be performed using a 0.40 mg/mL standard solution. The percentage relative standard deviation (%RSD) of retention time (RT) and peak area will be calculated using acceptance criteria of RSD ≤ 1% and RSD ≤ 2.5%, respectively.

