Greater effects have also been reported in patients with an inflammatory phenotype, suggesting that inflammatory status may modify the clinical effects of omega-3 fatty acids. These findings provide indirect support for a model in which baseline PUFA composition may be related to treatment outcomes through inflammatory and membrane-related pathways [11,12]. Nevertheless, evidence from supplementation studies does not establish that baseline PUFA concentrations predict response to conventional antidepressant medication.

Short-chain fatty acids (SCFAs), primarily acetate, propionate, and butyrate, are produced by the anaerobic fermentation of dietary fiber by the gut microbiota. After absorption into the systemic circulation, they may influence the gut–brain axis through effects on intestinal and blood–brain barrier integrity, G protein-coupled receptor signaling, immune regulation, and neurotransmitter-related pathways [13,14].

Experimental findings further suggest that SCFAs may affect microglial activation, pro-inflammatory cytokine production, and the expression of neurotrophic factors involved in synaptic plasticity [15,16]. These mechanisms remain incompletely characterized in humans but provide a plausible framework linking altered SCFA availability with depressive symptoms and potentially with treatment responsiveness.

Altered circulating and fecal SCFA profiles have been observed in individuals with major depressive disorder (MDD) compared with healthy controls, and lower concentrations of selected SCFAs have been associated with greater symptom severity [17,18]. In particular, reduced propionic acid concentrations have been reported in individuals with metabolic depression, suggesting that propionate may represent a marker of the metabolic and microbiota-related disturbances present in a subgroup of patients with depression [19]. Although these findings do not demonstrate predictive value, they identify baseline propionic acid as a biologically plausible candidate for further investigation.

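### The serum SCFA models leave inpatient or outpatient setting at blood draw as an optional adjustment, and as a main effect it would barely change the week-6 contrast

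*Protocol article*

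**What the plan says.** **SCFA time frame.** Section 2.4 contrasts erythrocyte fatty acids, which integrate the preceding 90–120 days, with SCFAs: "serum SCFAs represent dynamic, rapidly fluctuating metabolites produced by gut microbiota fermentation". It takes them as indicators of what the gut microbes are doing when the sample is drawn. Section 1.1 says that SCFAs "are produced by the anaerobic fermentation of dietary fiber by the gut microbiota". Blood is drawn once, fasting, in the morning.

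**Setting.** Section 2.3, explaining why adherence should be high, says: "As most participants will be inpatients at baseline". Section 2.1 names a teaching hospital, primary healthcare clinics and mental health clinics as recruitment sites. The sample is therefore mixed; no inpatient share is given. Enrolment is tied to the start of the antidepressant (within 5 days either side), not to admission.

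**Diet.** The FFQ-6 is "designed to evaluate habitual food consumption patterns over a specified retrospective period" (section 2.3). Of its indices the same section says: "These indices will serve as dietary covariates in regression analyses examining fatty acid profiles in relation to clinical outcomes".

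**Models.** In section 2.6 each acid has its own linear mixed model of BDI-II at baseline and weeks 3, 6 and 12. The terms are time, the standardized acid, acid-by-time, age, sex and antidepressant class, with a random intercept per participant. The primary contrast is the association of the acid with change to week 6. On sensitivity covariates it says: "These may include fish and seafood intake, a plant- and fiber-rich food index". Hospitalization status comes later in that list, and the section adds that the listed factors will not all be entered together.

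**The concern.** Patients on a ward and patients at home differ in food, activity and routine on the days before sampling. A marker of current gut microbial activity could differ between them for those reasons alone. Admission may also go with severity and with the course over the next six weeks. If both links exist, the SCFA slope partly separates inpatients from outpatients, whatever SCFAs themselves predict.

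Two features of the plan leave this open. Adjustment for setting is optional, and the natural way of adding it, as one more fixed effect beside age and sex, does not act on the primary contrast. The dietary adjustment describes habitual intake, which suits the erythrocyte acids but does not cover recent ward meals.

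The stakes are moderate. The pilot's stated product is effect-size estimates for sizing a later study (sections 1.2 and 3), and confounding does not shrink with a larger sample. Section 3 presents the SCFAs as the novel element, and its limitations do not mention setting.

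**Working it through.** The plan states no figure on this point, so there is nothing to reproduce. The check has two parts.

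**1. Does a main effect for hospitalization adjust the primary contrast?**

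Write the model for participant i at time t as

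y(i,t) = time(t) + b·x(i) + g(t)·x(i) + c·h(i) + u(i) + e(i,t),

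with x the standardized acid, h = 1 for inpatients and u the random intercept. The primary contrast is g(6) − g(0). The change score is

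y(i,6) − y(i,0) = [time(6) − time(0)] + [g(6) − g(0)]·x(i) + [e(i,6) − e(i,0)].

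The term c·h(i) cancels. With complete data and a random intercept, the acid-by-time contrast is estimated from within-participant differences, so a time-constant covariate cannot move it. With some missing visits the cancellation is no longer exact, but the effect stays minor. A term h(i)·time(t) does not cancel and does adjust the contrast.

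A simulation agrees (60 participants, 70% inpatients, SCFA shift 0.8 SD, 6-point setting difference in change, no true SCFA effect, 150 runs). The mean spurious week-6 slope was 0.79 without adjustment, 0.79 with a hospitalization main effect (identical to rounding error), and −0.12, which is zero within simulation error, with setting-by-time.

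**2. How large could the confounding be?**

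Every input is an assumption:
- p = 0.7, share of inpatients (the article says only that most are)
- d = 0.3 to 0.8, inpatient–outpatient difference in SCFA, in within-setting SDs
- D = 3 to 6, inpatient–outpatient difference in BDI-II change, in points
- residual SD of BDI-II change = 10

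With no true SCFA effect, the slope per total SD of SCFA is

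bias = p(1−p)·d·D / √(1 + p(1−p)·d²), with p(1−p) = 0.7 × 0.3 = 0.21.

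| d | D | numerator | denominator | bias |
|---|---|---|---|---|
| 0.3 | 3 | 0.21 × 0.3 × 3 = 0.189 | √(1 + 0.21 × 0.09) = 1.009 | 0.19 |
| 0.8 | 6 | 0.21 × 0.8 × 6 = 1.008 | √(1 + 0.21 × 0.64) = 1.065 | 0.95 |

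Standard error of the slope at n = 60: 10/√58 = 1.31. The bias is therefore 0.19/1.31 = 0.14 to 0.95/1.31 = 0.72 of one standard error.

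A wider grid (p = 0.60 to 0.90, d = 0.5 to 1.0, D = 3 to 6, SD 10) gives a bias of 0.13 to 1.29 points per SD. The simulated two-sided false-positive rate per unadjusted test is about 5% to 15%, against a nominal 5%. The bias falls as the inpatient share nears 100%; at d = 0.5 and D = 3 it goes from 0.35 (p = 0.60) to 0.13 (p = 0.90).

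**The case against.** The strongest reply is that the plan already foresees the issue. Hospitalization status is on the sensitivity list, antibiotics and probiotics are recorded, SCFAs are kept out of the principal component analysis, and a plant- and fiber-rich index is named separately from fish intake. All analyses are exploratory, and the article explains why not every factor can enter at n = 60. The assumed bias is below one standard error, and false discovery rate control is applied across acids. This limits the severity, and it stands. It does not answer the point that setting is optional and that a plain fixed effect would not act on the contrast of interest.

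Several stronger readings are tempting and are not supported:

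- **That the FFQ-6 mismatch is what confounds the primary SCFA result.** The primary model contains no diet term; the indices enter only in sensitivity models. Better-timed diet data would leave the primary estimate as it is. The missing setting term and the diet time frame are separate gaps.
- **That SCFAs reflect intake at the moment of sampling.** Section 2.4 refers to microbial activity, and the overnight fast limits the effect of the last meal. The link to diet runs through fiber fermentation.
- **That time on the ward is not recorded.** The article describes no such field, but it does not list the whole questionnaire, so absence cannot be concluded.
- **That a headline result is undermined.** No acid is singled out, and the size of any bias is unknown.

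It is also fair to say that setting could confound the erythrocyte acids, if they too differ between inpatients and outpatients. That argues for using the same analysis there, not for leaving it out for SCFAs.

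**Conclusion.** The point holds in a limited form. By the protocol's own account, SCFAs are momentary markers measured in a mix of mostly inpatients and some clinic patients. Neither the primary model nor any required analysis adjusts the week-6 contrast for setting, and the habitual-diet indices cannot do so indirectly.

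Confounding arises only if setting is related both to SCFA level and to week-6 change; if either link is absent the bias is zero. Under the assumed inputs it is small to modest: about 0.2 to 0.95 BDI-II points per SD, against a standard error of about 1.3. The documents supply none of these inputs. That a main effect does not adjust the contrast follows from the form of the model and not from those assumptions; it is exact with complete data. The change is worth making because it is cheap and uses a variable the plan already names. The SCFA analyses are not invalid without it.

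**What to change.** 1. For the three SCFAs, make a model with setting at blood draw (inpatient or outpatient) and setting-by-time a required analysis, reported beside the primary model. Preferably do the same for the erythrocyte acids, for consistency.
2. State in section 2.6 that any baseline covariate meant to adjust the acid-by-time contrast must enter with its own time interaction.
3. Make sure that the admission date is captured, so that days in hospital before sampling can be examined among inpatients.
4. State that, for SCFAs, FFQ-6 adjustment reflects habitual intake only.

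**Cost.** One date from the chart, if it is not already collected, and no extra visit or assay. With time as a four-level factor, setting and setting-by-time add up to four parameters per model (one main effect, three interactions). At 70% inpatients they rest on about 60 × 0.3 = 18 outpatients. The SCFA intervals widen slightly: at d = 0.8 by a factor of at most about √(1 + 0.21 × 0.64) = 1.065, before any gain from a smaller residual variance. If nearly everyone turns out to be an inpatient, the setting term will be poorly estimated, and the analysis of days in hospital becomes the more useful one.
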